**<http://www.controlled-trials.com/ISRCTN16488358/>**

## **PROTOCOL: ENHANCING THE QUALITY OF USER INVOLVED CARE PLANNING IN MENTAL HEALTH SERVICES (EQUIP)**

### **Research programme aims and objectives**

#### ***Aim***

The overall aim of the programme grant is to improve user and carer involvement in care planning in mental health services.

#### ***Major objectives***

- To develop, evaluate, implement and disseminate a user/carers-led training package for mental health professionals to improve the extent users and carers are involved in care planning.
- To develop and validate a patient reported outcome measure (PROM) to assess improvements in user/carers involvement
- To assess the clinical and cost effectiveness, feasibility and acceptability of this training package using a cluster randomised clinical control trial design.
- To identify the individual and organisational barriers and facilitators to implementing effective user and carer involvement in care planning.
- To use a multifaceted approach to comprehensively disseminate our findings.

These objectives are covered by four work streams incorporating seven studies.

This protocol is for work stream 2, study 5 which is the clinical randomised control trial (CRCT) and work stream 3, study 7 which is the process evaluation of the trial.

#### ***Work stream 1 (Studies 1-4)***

Develop a user/carers led training programme for mental health professionals and a measure of user/carers involvement in care planning.

### *Work stream 2 (Study 5)*

Evaluate the efficacy and cost effectiveness of user/carer involved care planning

### *Work stream 3 (Studies 6 -7)*

Implement user/carer involved care planning by understanding the individual and organisational barriers and facilitators and examine the processes involved in the development and use of user/carer involved care planning.

### *Work stream 4*

Disseminate user / carer involved training materials and resources for health professionals and users and carers of mental health services.

## **Background**

Involving service users in their care and providing choice is at the centre of policy initiatives aimed at improving quality of care. This principle is enshrined and prioritised in healthcare particularly mental health care policy and guidelines. There is a wealth of evidence that users and carers want significantly more involvement in the care planning process. However there is substantial empirical evidence that the majority of users and carers are marginalised in the care planning process.

## **Importance of proposed research**

This research is important because it provides an opportunity to make a quality improvement in mental health services which involves users and carers as co-producers of health care. Of importance is that such a quality improvement has the potential to be translated over both mental health and physical care settings and hence benefit many thousands of service users

## **Research team**

Our team is multidisciplinary with significant content, methodological, clinical, academic, lived experience and educational expertise.

## **Research environment**

The research will be undertaken in NHS settings (Manchester Mental Health and Social Care Trust and Nottinghamshire Healthcare NHS Trust, South West Yorkshire Partnership NHS Foundation Trust , Leicestershire Partnership NHT Trust) in collaboration with the Universities of Manchester and Nottingham.

## **Outputs and impact**

The outputs and impact of this programme grant have the potential to be substantial. We will have developed and delivered in partnership with users and carers a training programme to improve user and carer involvement in care planning. A user/carers patient reported outcome measure (PROM) will be developed and validated. We will know the effectiveness and cost effectiveness of user and carer involved care planning. We will have developed implementation guidelines based on our findings of the organisational and individual facilitators and barriers to user and carer involved care planning. We will develop tools to disseminate findings from the projects, including a care planning audit tool, user and carer materials for users and carers to empower them to facilitate change, and training materials which can be used across mental health services. We will offer these materials to up to ten NHS mental health trusts and advise on improving user and carer involved care planning.

## **Research governance**

The programme management group will meet every three months to discuss the progression and day to day management issues of the programme grant and will include the chief investigator (CI), all other investigators, and programme managers (PM). The CI will be responsible for the overall leadership, management and outputs of the programme. Each work stream will be led by a named work stream lead. The CI will maintain a log of the key milestones to be achieved against the timetable. Progress of these milestones and corresponding timetable will be reported at management meetings to ensure progression of the programme and to agree corrective action if necessary. The PMs will be responsible for the day to day running

and coordination of the programme and will be accountable to the CI. All research associates will be supervised by stream leads and overseen by the CI and site PIs.

### **Programme Steering Committee**

A programme steering committee (PSC) has been established and comprises an independent chair who has expertise in programme grants and care planning and three other independent members including a user representative who has had lived experience, a carer and a clinician who has expertise and experience of working in community teams. The composition of the PSC was agreed by the National Institute for Health Research (NIHR).

A full risk assessment of the programme has been conducted by the CI and PM. A risk register has been developed and potential risks of the study identified to enable any necessary mitigating actions to take place. A RAG rated system (Red, Amber, Green) is in place (in addition to a matrix measuring each risk on likelihood of risk occurring (low/medium/high) and impact if risk did occur. The risk register is managed and monitored by the PM and CI and is a standing agenda item at each programme management meeting.

### **Sponsorship**

Manchester Mental Health and Social Care Trust is the sponsor.

### **Service user and carer involvement**

We have extensive user and carer involvement. Within our NIHR funded programme development grant we argued that it was difficult for both users and carers and academics to work meaningfully together as users and carers were unfamiliar with research methods and concepts. To overcome this we ran a successful six day interactive research methods course which resulted in positive feedback from users and carers. Many of the applicants were responsible for teaching their areas of expertise (e.g. [name] – qualitative research; [name] – health economics; [name] - literature searching and trial design). We taught the course at a similar level to our MRes but worked in small groups with up to three facilitators. The course was devised and led by [name] (Co-Investigator)

and [name] (CI). The course has been cited by the Mental Health Research Network (MHRN) as an exemplar of good practice. In addition we ran a half day workshop explaining the nature of programme grants and shared our thoughts on the proposed grant and obtained helpful feedback. A full day meeting of users and carers and the trial team was conducted to determine the measures for the evaluation phase.

We have identified a range of roles for the service users and carers who have participated in the programme development grant. We have a large advisory group (n=16) of users and carers, and two service users and one carer are formal co-applicants and have worked with the research team to co-facilitate focus groups and interviews during EQUIP studies 1 and 2. One further service user is also a member of the programme steering committee. Users and carers will be participating in the overall management of the research, in developing participant information resources, undertaking and analysing the research, contributing to the reporting of the study report and in the dissemination of research findings.

## **Aims**

### ***Work stream 2 (Months 18-48)***

The aim of this work package is to evaluate the efficacy and cost effectiveness of a user/carer involved training package developed earlier in the programme grant.

This aim will be achieved through the undertaking of study 5.

#### *Study 5*

- To determine if a user/carer led training package is effective in increasing user/carer involvement in care planning and improving health outcomes for service users with severe mental illness under the care of community teams.
- To determine if a user/carer led training package is cost-effective in improving short term health outcomes for service users with severe mental illness under the care of community teams.

### ***Work stream 3 (Months 0-48)***

The aim of this work package is to understand professionals' and users/carer perspectives about the factors that inhibit or promote user involvement and the integration of care planning into clinical settings. Furthermore, the package will investigate the impact of the training package to enhance user involvement in care planning.

The aim will be achieved through the undertaking of two studies (study 6 and 7):

#### *Study 6*

Conduct a mapping exercise in organisational structures and policies related to care planning which is reviewed and updated over the course of the project (approved by Manchester University Research Ethics Committee ref: 13304).

#### *Study 7:*

The aims of this study are to examine: (i) how user/carer involved care planning training and its principles impacts on and is incorporated into existing routine clinical practices; (ii) how care planning affects the way in which professionals relate to, communicate with and negotiate therapeutic options with users; (iii) how the new care planning training and arrangements impact on existing methods of coping, self-care and the development of service user expertise and how it shapes and transforms relationships between service users and professionals; (iv) the impact on networks, a sense of control, security and identity compared to previous care planning practices; (v) service users' perceptions of their preparation and support in relation to engaging with the form and content of the new system of care planning and its benefits and use .

The objectives are to examine:

- How training for user involved care planning and its principles impacts on and is incorporated into existing routine clinical practices;
- How care planning affects the way in which professionals relate to, communicate with and negotiate therapeutic options with users;
- How the new care planning training and arrangements impact on existing methods of coping, self-care and the development of service user expertise and how it shapes and transforms relationships between service users and professionals;
- The impact of training on service users' perceptions of networks, a sense of control, security and identity compared to previous care planning practices;
- Service users' perceptions of their preparation and support in relation to engaging with the form and content of the new system of care planning.

## **Background**

### ***Study 5***

The full programme grant application describes the background to the need for the programme as emanating from the observation of the increased importance being attributed to involving service users in their care, whilst at the same time the majority of service users and carers still feeling marginalised in the care planning process. There is evidence that service users and carers want significantly more involvement in the care planning process, but this is not always achieved (DoH 2000, Royal College of Physicians 2009). There are inconsistencies in practice, and embedded within this

there is poor communication (Healthcare commission 2008). Compounding these problems, there are also problems with the quality of the relationships with and between professionals at all levels (Blenkiron et al 2003, Bramesfeld et al 2007, Mind 2010).

This research is important because it seeks to develop a standardised training package to achieve better care planning, and to test the efficacy and cost effectiveness of this package. It will provide an opportunity to improve the quality of mental health care across community and rehabilitation inpatient mental health services.

## **Study 7**

A process evaluation of the training programme delivered as part of the trial is deemed appropriate because successful implementation of the user/carer led care planning implicates a range of factors including the integrity of the intervention and the acceptability of the intervention to both clinicians and service users (Greenhalgh et al, 2005). This current study is designed to explore how far the user/carer led care planning has been taken up by and implemented in the daily work of the health professionals who attended the training and what the consequences of this uptake has been. It will complement and supplement the evidence provided by the main randomised trial (as recommended by the MRC framework for evaluation of complex intervention, Campbell et al, 2000).

Where results from the trial are positive, the process evaluation will consider the conditions, mechanisms and processes that gave rise to this success to help translation into other areas. Conversely, if findings are negative or inconclusive, the process evaluation can examine the sources or barriers to implementation and consider why these negative results are observed.

## **Method**

### ***Study 5***

#### *Study Design*

The study will adopt a cluster randomised trial design. The training package will be delivered to clinical staff working in community teams. A cluster design is required to avoid contamination.

We will adopt a mixed design, including both a 'cluster cohort' design, and a 'cluster cross sectional' design (see Figure 1 for an outline of the design, and Figure 2 for the CONSORT flow diagram).

In the 'cluster cohort' design, we will recruit service users cared for by each community team and conduct a detailed face-to-face assessment at baseline. Each community team will then be randomised to either intervention (training in care planning) or control (usual care planning). We will then train the intervention community teams in care planning, and conduct another detailed face to face assessment with the same service users 6 months after the baseline assessment.

The design will also include a 'cluster cross sectional' element. Six months after randomisation, we will distribute a questionnaire to all service users who are not part of the 'cluster cohort' but who are under the care of all community teams using a simple postal questionnaire.

The advantages of the design are outlined in Box 1.

**Box 1 Advantages of the mixed design**

The 'cluster cohort' design allows more accurate adjustment for baseline characteristics at an individual level, giving increased statistical power.

However, for the cluster cohort, service users need to participate in two relatively long face to face assessments, which may be burdensome to service users or difficult to organise if people move often. This means the cluster cohort may be vulnerable to recruitment issues (where only a small number of eligible service users take part) and attrition (i.e. where service users do not attend for follow-up), both reducing external validity.

The 'cluster cross-sectional' design can help ameliorate these problems. Service users only have to agree to assessment once, and the assessment is designed to be less burdensome as it includes fewer measures. This means that a higher proportion of patients may agree to take part and be retained in the study, potentially increasing the sample size and the external validity of the results. However, it will tend to have less power due to the reduced ability for baseline adjustment. We will sample a proportion of eligible service users for the 'cluster cross-sectional' design to reduce cost and administrative burden.

Adoption of the combined design provides protection against problems in either of the individual approaches.

A potential threat to the validity of a cluster randomised trial is recruitment bias, where professionals allocated to different trial arms recruit differently depending on their allocation, leading to selection bias and baseline incomparability (Torgerson 2001). Whilst it is preferable to recruit patients prior to allocation, the logistics of the trial means that clusters will need advance notice of their training date, which will require us to inform them of their allocation. However, initial patient selection in the EQUIP trial is not by professional referral, but will use existing registers of patients. This will be undertaken by the Mental Health Research Network (MHRN), Clinical Studies Officer (CSO). This will limit the ability of professionals to influence recruitment, as their only impact will be to exclude patients. We will stress the importance of including all eligible patients, provide guidance on exclusion criteria and report details of all exclusions by trial arm in the study report.

Once service users have been recruited, the clusters will be allocated randomly to either intervention or control. To reduce selection bias, allocation will be determined through an external telephone randomisation service at the Clinical Trials Unit of the Manchester Academic Health Science Centre. Clusters will be submitted to the randomisation service in pairs. Each pair will be from the same site (Manchester/Nottingham/SW Yorkshire/Leicestershire) and similarly matched in other characteristics where possible. One member of the pair will be allocated to intervention by random selection, the other allocated to control. To reduce detection bias, we will seek to blind researchers undertaking assessments of the quality of care planning to the group to which clusters have been allocated. We will report the success or otherwise of our attempts at blinding.

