## **Study setting and sample size**

### ***Study 5***

#### *Recruitment and randomisation of community teams and rehabilitation inpatient facilities*

Twenty four community teams will be recruited, from several different geographical areas (Manchester, Nottingham, South West Yorkshire and Leicestershire). All community teams in each geographical area will be eligible for inclusion. Community teams will be randomly allocated to receive the user/carer-led training package in care planning or to continue with usual practice.

Recruitment and training will be undertaken in sequence, to maximise efficiency in delivery of training to community teams, but also to ensure there is sufficient time to permit the relevant baseline assessments to be undertaken with service users, cared for by each community team.

We will obtain lists of service users from community teams and then the teams (clusters) will be randomised. Around the same time as randomisation (but before

the training intervention has occurred), the service users will be contacted by postal invite with one follow up phone call (using the lists provided), consent obtained and baseline assessments undertaken. This is to ensure that there is a maximum period of time between the baseline assessment and the six month follow up assessment. The baseline assessment will therefore be scheduled to be undertaken as close to the training (intervention) as possible and will occur in a maximum six week period prior to the community teams being trained. Service users will be followed up six months from the baseline assessment point, aiming for follow-up assessments within two weeks of the six month deadline.

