### *Recruitment of service users/carers*

To recruit service users in the 'cluster cohort', the direct care team within the community team (cluster) will produce a list of all patients who meet eligibility to participate in the trial, including any reasons for exclusions. This will be referred to as a list of their 'caseload'. These patient lists will be used by the MHRN CSO (or admin support within the Trust) to send out an introductory letter, participant information sheet and consent to contact form to each patient (appendix 6), inviting them to take part in the study. Patients will be required to 'opt in' by returning the consent to contact form in a pre-paid envelope to the research team. CSOs will contact non responders by telephone on one occasion to allow patients to opt in over the telephone. Some Trusts prefer that the initial distribution of introductory letter and participant information sheet and consent to contact form be carried out by a clinician during a routine meeting with the service user. Where this is the preferred approach, the clinician will introduce the study to the service user and give them the information pack. The clinician will discuss participation with the service user and if the service users wishes to be contacted by a university researcher to receive more information and discuss participation in the trial, the clinician will complete the

consent to contact form with the service user and pass it to the research team. This will be done by secure fax or over the telephone.

The research team will then follow up the consent to contact forms, to answer any further questions, and when a participant is recruited, the researcher will continue with a face to face informed consent process. Following signed consent, all baseline measures will be completed (table 1). In some sites CSO may be available to support with data collection. Where this is the case they will be trained by the research team with regard to collecting data and follow their own NHS Trust Lone Worker procedures.

Service users will be asked at the informed consent meeting to nominate a carer to be included in the study and if they choose to do so, will be provided with a questionnaire pack (including introductory letter, information sheet, questionnaire, pre-paid envelope and consent to contact at follow up form).

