To recruit service users in the 'cluster cross sectional' study, we will conduct a postal survey of all service users under the care of each community teams six months after randomisation, excluding those already recruited to the 'cluster cohort'.

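### The protocol gives two incompatible orders for recruitment and team allocation, and its stated safeguard against recruitment bias is contradicted by its own recruitment procedure

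*Protocol*

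**What the plan says.** **Order of events.** Under Method, Study 5, Study Design, service users are recruited and assessed face to face, and teams are randomised afterwards. The allocation paragraph after Box 1 repeats the order: "Once service users have been recruited, the clusters will be allocated randomly to either intervention or control".

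Box 1 itself grants that recruiting before allocation would be preferable, but says that "clusters will need advance notice of their training date, which will require us to inform them of their allocation". The section Recruitment and randomisation of community teams and rehabilitation inpatient facilities says "We will obtain lists of service users from community teams and then the teams (clusters) will be randomised", with contact, consent and baseline assessment at about the time of randomisation and before training.

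**Safeguard.** Box 1 names recruitment bias as a threat and answers that "initial patient selection in the EQUIP trial is not by professional referral". The Clinical Studies Officer (CSO) works from existing registers, and exclusion is said to be the only influence professionals have. The Service user/carer consent section likewise makes CSOs responsible for determining eligibility and for mailing.

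**Procedure.** Under Recruitment of service users/carers, the direct care team produces the list of eligible patients with reasons for exclusions. The default route is a mailed pack and one CSO telephone call to non-responders. Some Trusts prefer that a clinician present the study at a routine meeting. There, "The clinician will discuss participation with the service user", completes the consent to contact form with them and passes it to the research team.

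**The concern.** A site reading Study Design would finish recruitment before its teams are randomised. A site reading Box 1 could invite service users after the team knows its arm. Both would be following the protocol.

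The order matters because of who does the inviting. If a clinician knows that the team is about to be trained, or is a control, the effort put into encouraging particular service users to opt in can differ by arm. Recruitment is opt-in, with 10 to 30 service users per team, so there is room for this. The primary outcome, HCCQ-10, is the service user's own rating of how far their care supports autonomy, so a difference in who opts in bears directly on the endpoint. The trial's stated protection is that professionals can only exclude, and the clinician route does not satisfy that description.

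**Working it through.** **Step 1: the order of events, side by side**

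| Section | Order given |
|---|---|
| Study Design | recruit, baseline assessment, randomise |
| Allocation paragraph after Box 1 | recruit, randomise |
| Box 1 | recruiting first is preferable, but teams must be told their allocation ahead of training |
| Recruitment and randomisation of community teams | lists, randomise; contact, consent and baseline at about that time, before training |

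Reading *recruited* in the allocation paragraph as merely *listed* does not reconcile these, because Study Design puts the face-to-face baseline assessment before randomisation. The four statements cannot all describe one cohort.

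**Step 2: the safeguard against the procedure**

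| Box 1 and consent section | Recruitment of service users/carers |
|---|---|
| selection by the CSO from registers; CSO determines eligibility | care team produces the eligible list |
| professionals can only exclude | in some Trusts the clinician presents the study, discusses it and completes the contact form |

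The right-hand column describes influence over who opts in. Reporting exclusions by arm would not reveal it.

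**Step 3: the protocol's own power figure**

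Inputs from Sample size: 12 teams per arm, mean 20 per team, 80% follow-up, ICC 0.05, effect 0.4 SD. Two-sided alpha of 0.05 is assumed, as none is stated.

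- Followed up per team: 20 × 0.8 = 16; per arm 12 × 16 = 192
- Design effect: 1 + (16 − 1) × 0.05 = 1.75
- Effective n per arm: 192 / 1.75 = 109.7
- Power: 84.2% (normal), or 80.8% (t with 22 df)

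The stated power above 80% reproduces and is not in question.

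**Step 4: what an unremoved shift would do**

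The document gives no size for any recruitment bias, so the bias inputs here are assumptions.

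- Unadjusted SE: √(2 × 1.75 / 192) = 0.135 SD
- Adjusted SE, assuming a baseline to six-month correlation of r = 0.5, so a variance factor of 1 − 0.25 = 0.75: √(2 × 0.75 × (0.05 + 0.95/16) / 12) = 0.117 SD
- Residual shift b = assumed shift among clinician-route recruits × share recruited by that route × fraction left after baseline adjustment
- Type I error = P(|Z + b/0.117| > 1.96)

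| Assumed inputs | b (SD) | Type I error |
|---|---|---|
| adjustment removes all of the shift | 0 | 5% |
| 0.3 × 0.25 × 0.5 | 0.0375 | about 6.2% |
| 0.3 × 0.5 × 0.5 | 0.075 | 9.8% |
| 0.3 × 1 × 0.5 | 0.15 | 25.0% |

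With the unadjusted SE of 0.135, shifts of 0.10 and 0.15 SD give 11.5% and 19.9%.

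**The case against.** The protocol does more than the contradiction suggests. Lists, with reasons for exclusion, are obtained before randomisation, so their composition is largely protected. Post plus one CSO call is the default, and the clinician route applies only in some Trusts. Even there the research team answers questions and takes written consent, and baseline precedes training. Exclusions are to be reported by arm. The analysis adjusts for baseline HCCQ; if clinicians selected on the current relationship, which that baseline measures, little bias might remain. Teams are paired within site, so a Trust's preferred route would usually operate in both arms. All of this stands as a limit on the risk. None of it settles which order applies or fully covers unequal encouragement to opt in.

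Three stronger readings are tempting but unsupported:

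- *The safeguard fails altogether.* It does not: the list-before-randomisation step and the postal route survive. Nor does any section say that allocation is disclosed before the clinician approach; the text leaves it open.
- *Type I error is 10% to 25%.* That needs a 0.3 SD shift, at least half of recruits coming through clinicians, and adjustment removing only half. None of these has a source in the protocol. A quarter of recruits gives about 6%, and complete adjustment gives 5%.
- *The postal survey frame is defective as well.* The protocol plans that "we will conduct a postal survey of all service users under the care of each community teams six months after randomisation", leaving out cohort members. Surveying the current caseload is a legitimate cross-sectional choice. Nothing in the document suggests that staff training changes who joins or leaves a caseload, and the cohort estimate is presented separately.

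**Conclusion.** The point holds as an error in the current text. Recruitment is placed before randomisation in two places and not in two others, and the claim that professionals can only exclude is untrue of the procedure allowed in some Trusts. What remains exposed is differential encouragement by clinicians who may know their team's allocation.

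Confidence is high for the contradictions and low for any resulting bias, whose size and direction cannot be derived from the document. The range of 5% to about 25% for type I error is illustrative. It rests on residual shifts of 0 to 0.15 SD, r = 0.5, ICC 0.05, 16 followed up per team and a two-sided 5% test. It shows that even a modest unremoved shift would matter beside a 0.4 SD target. Unequal opt-in is hard to repair at analysis, so the sequence should be settled in the protocol.

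**What to change.** 1. State one sequence, in the same terms, in Study Design, Box 1 and the allocation paragraph after it, the section on recruitment and randomisation of teams, and Recruitment of service users/carers. Say who knows the allocation when invitations are made.
2. Lodge each pair's eligible list and exclusions with the trials unit before the pair is randomised, with no later changes. This makes binding what the protocol already half-provides.
3. Complete any clinician-led approach before allocation is disclosed to the team. After disclosure, invite only through the CSO, by post or telephone.
4. Correct the Box 1 sentence on professionals' influence, and align the consent and recruitment sections on who determines eligibility.
5. Report recruitment route, numbers approached and uptake by arm, alongside the exclusions already promised.

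**Cost.** A protocol amendment and some extra logging. Trusts that prefer the clinician approach must bring it forward or give it up. Where disclosure is delayed to accommodate it, teams get shorter notice of training, which is awkward because training is planned to start straight after baseline recruitment. Teams using only the CSO route can still be told early.
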